### 2.3. Participants

Participant selection allows the randomization of the sample following the natural ordering of the rehabilitation service where the study is carried out. The assignment of children to their different therapists is performed according to the available treatment times of the latter. In other words, patients are assigned to one treatment or another following criteria of immediacy as part of the regular routine of the rehabilitation service. Therefore, the randomization will be carried out through the needs of the service, as is already the case.

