## 3. Methods and Timeline

Phase 1. Initial Assessment: Children who go to the rehabilitation center where they have been referred will be treated, an initial routine clinical examination will be performed, including: Personal/medical data collection.GMFM quantification.Treatment with the physiotherapist.Training of the parents in the home program.Recording for the IMP quantification.

Phase 2. Intervention period (2 months): The assignment to the therapist will be randomized according to the needs of the service, where each therapist will adapt the treatment according to the initial assessment. Both assessors and therapist cannot be blinded to the allocation or treatment, and both required live-direct performance. An external assessor (blind to both) will be able to score the IMP recordings. 

Children will receive weekly or fortnightly treatment, and their parents, family members, or carer will be trained in carrying out a home program. Each therapist will adapt the treatment according to the initial evaluation, as is usually performed in the rehabilitation service. During the treatment sessions, the physiotherapist will apply the therapy directly, either based on Vojta therapy or conventional physiotherapy. The frequency of repetition of the treatment at home and in the hospital will be recorded, depending on the availability of each family and the normal functioning of the service.

Phase 3. Second assessment at 2 months (±1 week, depending on follow up appointments).

Collection of data on the possible changes made in previous treatments and the frequency of home treatment (possible incidents due to illness or family limitations).GMFM quantification.Recording necessary for IMP quantification.

Children carried on clinically with the intervention, but this short period would allow us to attribute changes to RL, controlling better the influence of other factor (such as age maturation or other therapy inputs).

Study length. The data collection will be carried out for 4 years from the approval of the CEI. Only patients receiving healthcare with any of the therapies under investigation after authorization by the CEI will be included.

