### Statistical Methods

Statistical analysis will be performed using the SPSS 27.0 statistical software for Windows (SPSS Inc., Chicago, IL, USA; version 27.0). The normality of the sample will be checked using the Shapiro–Wilk test, and if it follows a normal distribution, an analysis of variance (ANOVA) of repeated measures p will be used, with time (pre-treatment and post-treatment) as an intra-group factor, and Vojta and conventional physiotherapy groups as the inter-group factor, all with a Bonferroni correction. Statistical analysis will be performed with a confidence level of 95%, so a *p*-value of <0.05 will be considered significant.

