The rate values are calculated by dividing the total score by the time (days of age) required to achieve it, assuming that the neonatal GMFM would be zero. The acceleration factor is calculated by dividing the differences between final and initial rate (assumed to be zero at birth), by the age in days (elapsed time). The same rate and acceleration factors of acquisition are figured out between the initial assessment and after two months of the intervention. Only new points acquired during this period were considered to calculate the rate of development and acceleration values in the intervention period. Because the distribution of the item acquisition during the pre-intervention period is unknown, we performed a second rate calculation assuming that all the items were adquired during the last two months before the intervention (for children older than 2 months at initial assessment). This simulation of the maximal possible pre-intervention rate and acceleration will limit the possibility of being overcome by the post-treatment values and will avoid average values slowing down the last two preintervention months. Completing all the items in the previous two months is unlikely and would make it more difficult to obtain improvements after the intervention, especially for the older children. Even if these calculations do not benefit our results, they will ensure that the rate and acceleration post-intervention can be compared within same-lasting and following periods. We know that the GMFM item acquisition is not linear, and both calculations will help us to understand if the rate differences are due to natural acceleration or a significant therapeutic change. On the other hand, this will avoid comparing low average rate values due to longer pre-intervention periods and, therefore, random positive outcomes. Rate values within each GMFM dimension will then be considered and will help to clarify the results. 

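### If the maximal pre-intervention rate enters the group-by-time test, the comparison of arms equals the treatment effect minus the baseline difference; the rate is conservative only within a child

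*Protocol article*

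**What the plan says.** The Discussion (section 4) defines two pre-intervention rates. The first divides the baseline GMFM total by age, "assuming that the neonatal GMFM would be zero". For children older than two months at the first assessment there is a second: "we performed a second rate calculation assuming that all the items were adquired during the last two months before the intervention". On the post side, "Only new points acquired during this period were considered to calculate the rate of development and acceleration values in the intervention period". Follow-up is of the same length: "Second assessment at 2 months (±1 week, depending on follow up appointments").

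The second calculation is offered as a strict test: "This simulation of the maximal possible pre-intervention rate and acceleration will limit the possibility of being overcome by the post-treatment values". The same paragraph adds: "Even if these calculations do not benefit our results, they will ensure that the rate and acceleration post-intervention can be compared within same-lasting and following" spans of time. It also gives both calculations the task of showing whether rate differences reflect natural acceleration or a therapeutic change.

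Section 2.6 says that rates, not net scores, are considered. The Statistical Methods section gives one test, a repeated-measures ANOVA "with time (pre-treatment and post-treatment) as an intra-group factor, and Vojta and conventional physiotherapy groups as the inter-group factor". It does not say which variable is analysed. On allocation, section 2.3 says that "patients are assigned to one treatment or another following criteria of immediacy as part of the regular routine of the rehabilitation service".

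**The concern.** A penalty that is strict for one child need not be strict for a comparison of two groups. Crediting the whole baseline score to two months raises the hurdle in both arms. In a group-by-time test the shared part of that hurdle cancels, and what remains is the difference in baseline score between arms. A calculation meant to separate natural from therapeutic change could then support a Vojta effect that is absent or hide one that is present. Even with balanced arms it adds the baseline variance to the error. Children are aged 0 to 36 months, so baseline scores can be expected to vary widely.

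**Working it through.** **Inputs.** From the protocol: 30 children per arm (section 2.6), significance level 0.05 (Statistical Methods), both periods T = 2 months. The protocol gives no SD, effect size or power for this rate, so there is no figure of its own to reproduce. Assumed: SD of the two-month gain SDg = 5 points, baseline SD0 = 10, 15 or 20 points, correlation ρ = 0 or 0.3 between gain and baseline, true effect 4 points, two-sided test, no ceiling.

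**1. What the contrast is.** Let S be the baseline score and D the new points in the two months, so the two-month score is S + D. The pre rate is S/T and the post rate is D/T.

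Post − pre = (D − S)/T = (two-month score − 2S)/T.

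With two time points and two groups, the group-by-time F test is the squared two-sample t test on post − pre. Its expectation, times T, is the arm difference in D minus the arm difference in S. This step needs no assumed SD. The acceleration version is built from the same rates, so it carries S as well.

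**2. Example.** Two children each gain 6 points in 60 days, from baselines of 30 and 20.
- (6 − 30)/60 = −0.40 per day
- (6 − 20)/60 = −0.23 per day

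The gain is equal, yet the lower starter looks better.

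**3. Balanced arms.** SD of (D − S) = √(SDg² + SD0² − 2ρ·SDg·SD0). Type I error is 5%, because baseline then acts only as noise (4.9% in simulation). Power by noncentral t for a 4-point effect:

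| SD0 | ρ | SD of D − S | Power, maximal rate | Power, new points alone |
|---|---|---|---|---|
| 10 | 0 | 11.2 | 27.6% | 86% |
| 10 | 0.3 | 9.7 | 34.6% | 86% |
| 15 | 0 | 15.8 | 16.1% | 86% |
| 15 | 0.3 | 14.3 | 18.6% | 86% |
| 20 | 0 | 20.6 | 11.5% | 86% |
| 20 | 0.3 | 19.1 | 12.5% | 86% |

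Power is lost whenever SD0 > 2ρ·SDg. There is none to lose if, for example, SD0 = SDg and ρ = 0.5.

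**4. No treatment effect, Vojta baseline 0.5 SD0 lower.** If gain does not follow the gap, the contrast is shifted by 0.5·SD0. If gain follows baseline with slope b = ρ·SDg/SD0, the shift is 0.5·SD0·(1 − b). For SD0 = 10 and ρ = 0.3: b = 0.15, shift = 5 × 0.85 = 4.25.

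| SD0 | ρ | Gain not shifted | Gain follows baseline |
|---|---|---|---|
| 10 | 0 | 39.9% | 39.9% |
| 10 | 0.3 | 49.8% | 38.3% |
| 15 | 0 | 43.9% | 43.9% |
| 15 | 0.3 | 51.4% | 43.5% |
| 20 | 0 | 45.5% | 45.5% |
| 20 | 0.3 | 51.3% | 45.4% |

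New points alone give 5.0% if gain is not shifted and 8.8% if it follows baseline at ρ = 0.3. With a gap of 0.25 SD0 the maximal-rate contrast gives about 13–17%.

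**5. The other direction.** With SD0 = 15, a Vojta baseline 7.5 points higher and a real effect of 3.7 points, the expected contrast is 3.7 − 7.5 = −3.8. In simulation (ρ = 0) it favoured Vojta significantly in 0.2% of trials.

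**6. The alternative.** In the same simulation (SD0 = 15, ρ = 0, 30 per arm), regressing the two-month score on arm and baseline gave 5.1% false positives under a 7.5-point gap, against 43% for the maximal rate. With balanced arms and the 3.7-point effect its power was 80%, against 14.5%.

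**The case against.** The ANOVA's dependent variable is unnamed, and the maximal rate appears only in the Discussion, as a simulation beside the first rate. Its wording is about pre-treatment and post-treatment periods, and section 2.3.2 says each child is compared only with itself. For that use the calculation is conservative, and the authors may intend nothing more. This stands, and it makes the point conditional. It does not remove it: the ANOVA is the only test described, it compares the arms, section 2.6 restricts analysis to rates, and both calculations are used to identify a therapeutic change.

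Several stronger readings are tempting, and the documents do not support them.
- *The protocol promises that this calculation cannot help its own results.* The words in "Even if these calculations do not benefit our results, they will ensure that the rate and acceleration post-intervention can be compared within same-lasting and following" are a concession, not a guarantee. The remark nearby about chance positive findings concerns long pre-intervention periods, not arms.
- *The test is biased towards Vojta.* The direction depends on which arm starts lower, and no baseline data are given. Availability-based allocation does not assure balance, but nothing shows that it tracks age or severity.
- *Power is bound to collapse.* The loss depends on SDs that the protocol does not state.
- *The protocol is deficient for not specifying baseline adjustment.* That can be left to an analysis plan. The point here is the defined rate and the property attached to it.

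**Conclusion.** The point holds in conditional form. That the contrast equals (two-month score − 2 × baseline score)/2 months follows from the protocol's own definitions, given two equal periods and a child older than two months at baseline. That this rate enters the ANOVA is a well-supported inference, not a stated fact. If it does, the protection that the Discussion describes holds within a child and does not carry over to the comparison of arms. A baseline gap biases the result either way. Without a gap the type I error is correct, and the usual cost is power. The sizes (38–51% false positives at an imposed 0.5 SD gap, 11–35% power for a 4-point effect) are illustrations under assumed SDs. A score accumulated over up to 36 months should vary more than a two-month gain, so a substantial loss is plausible but not documented.

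**What to change.** In Statistical Methods, name the dependent variable and state that the maximal rate and its acceleration do not enter the group-by-time test. In section 4, keep them as a within-child description, say that they are conservative only within a child, and do not use them to separate natural from therapeutic change between arms. Compare the arms by regressing new GMFM points over the two months on group, baseline score and age. Raw gain alone is not quite enough, since it too drifts (to about 9% above) when gain depends on baseline.

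The cost is wording in two sections and one regression on data already being collected, with no extra children, visits or staff. The small loss is the maximal-rate version as a between-arm check.

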### 2.4. Outcomes

Two of the most accepted scales in pediatric rehabilitation will be used, quantifying gross motor function from different aspects.

The first is the Gross Motor Function Measure (GMFM). Gross motor function and mobility have important roles for classification, assessment, and research involving children with neuromotor disorders [42,43,44]. The Gross Motor Function Measure [45] could be currently considered as gold standard for the quantification of gross motor function in the pediatric rehabilitation. These follow ups of thousands of children with cerebral palsy described the long-term development of their gross motor function and defined five unalterable levels of severity. By the age of six, stability over time on the prognosticated level of mobility is expected [45]. Even though the GMFM was not designed to assess outcomes of therapeutic interventions, some authors have used its centiles to compare individual effects. The use of the reference percentiles for the GMFM as outcome make it possible to estimate the change between two subsequent assessments and to directly compare gross motor improvement across ages and Gross Motor Function Classification System (GMFCS) levels. On the other hand, uncompleted items of GMFM assessments are used as short-term therapeutic goals and, therefore, individually controlled comparison of the rate of acquisition of gross motor function seems to be possible within each range. 

The Infant Motor Profile (IMP) scale [46] is another evidence-based method of assessing infant motor behavior. It not only quantifies motor milestones, but also tests movement quality by analyzing five factors: variability, adaptation, symmetry, fluency, and capacity. The advantage of this scale is that the assessment is performed through video recording, allowing us to have a dedicated clinical evaluator blinded to the type of intervention. 

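### Because the treatment-period GMFM rate counts only new points, a dimension completed at baseline must show a slow-down, and above about half the scale no gain can exceed the maximal pre-rate

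*Protocol article*

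**What the plan says.** Section 4 of the protocol article defines the rates. Before the intervention: "The rate values are calculated by dividing the total score by the time (days of age) required to achieve it". The score at birth is taken as zero. During the intervention: "Only new points acquired during this period were considered to calculate the rate of development and acceleration values in the intervention period".

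A second pre-intervention rate is added: "we performed a second rate calculation assuming that all the items were adquired during the last two months before the intervention", applied "for children older than 2 months at initial assessment". The article presents it as a simulation of the highest possible pre-rate. It concedes that the assumption is unlikely and makes improvement harder to show, above all in older children. Of the calculations it says "they will ensure that the rate and acceleration post-intervention can be compared within same-lasting and following periods".

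The same section then takes the rates to the individual dimensions: "Rate values within each GMFM dimension will then be considered and will help to clarify the results".

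Three other places matter:
- Section 2.4 shows that the item set can be exhausted: "uncompleted items of GMFM assessments are used as short-term therapeutic goals".
- Section 2.6 sets the raw scores aside and analyses only the rates.
- The Statistical Methods part of section 3 names a repeated-measures ANOVA with time (pre/post) and group as its factors.

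**The concern.** The pre-rate rewards everything the child has achieved, while the treatment-period rate can reward only what is left to achieve. On a finite item list these two quantities pull in opposite directions: the more a child can do at entry, the higher the bar and the smaller the room to clear it. For a completed dimension the sign of the change is settled before treatment starts. For a child above a certain share of the scale, the same holds for the comparison with the maximal pre-rate.

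Entry runs from 0 to 36 months (section 2.3.1), so children may complete dimensions at different times relative to entry. The within-child comparison matters here because section 2.3.2 justifies its handling of concomitant treatment by saying that each child serves as its own comparison. Forced slow-downs enter that comparison directly. They enter the group comparison too if the arms differ in baseline function. Section 2.3 assigns children by therapists' available treatment times, which does not protect against such a difference. The dimension results, which are meant to clarify the findings, would be least informative in the dimensions that most children have already completed.

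**Working it through.** The plan gives no figure of its own on this point, so there is none to reproduce. The check is algebra on the stated definitions.

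**Inputs**
- S = GMFM score at baseline and A = age at baseline, with score zero at birth. First pre-rate = S/A (section 4).
- W = two months. Second pre-rate = S/W (section 4).
- N = new points over the intervention period T. Treatment-period rate = N/T (section 4), with T = 2 months ±1 week (section 3, Phase 3).
- M = maximum of the scale or dimension, so N cannot exceed M − S. The article does not state M, but it cancels below.

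**Step 1: completed dimension.** S = M, so N = 0. The treatment-period rate is 0/T = 0, against a pre-rate of M/A or M/W, both above zero. Both calculations show a slow-down.

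**Step 2: second calculation.** The later rate exceeds the pre-rate only if N/T > S/W. With the best possible gain, (M − S)/T > S/W, which gives S/M < W/(W + T).
- Equal windows: S/M < 0.50. The gain must exceed the whole baseline score.
- Visit one week early (60.9 and 53.9 days): 60.9/114.8 = 0.53.
- Visit one week late (60.9 and 67.9 days): 60.9/128.8 = 0.47.

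On an assumed 0–100 scale with equal windows, in points per month:

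| Baseline | Maximal pre-rate | Best possible later rate |
|---|---|---|
| 45 | 45/2 = 22.5 | 55/2 = 27.5 |
| 55 | 55/2 = 27.5 | 45/2 = 22.5 |
| 70 | 70/2 = 35 | 30/2 = 15 |
| 90 | 90/2 = 45 | 10/2 = 5 |

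Age does not appear in this condition. It depends on baseline score alone.

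**Step 3: first calculation.** The same argument gives S/M < A/(A + T). With T = 2 months:
- 3 months of age: 3/5 = 0.60
- 6 months: 6/8 = 0.75
- 12 months: 12/14 = 0.857
- 24 months: 24/26 = 0.923
- 36 months: 36/38 = 0.947

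Here the limit binds only near the top of the scale in older children.

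**Step 4: acceleration with the maximal pre-rate.** If the treatment period is taken to start from rate zero, the condition is N > S, a cut-off of M/2. If it starts from the pre-rate, it is (N/T − S/W)/T > S/W², that is N > 2S with equal windows, a cut-off of M/3. The text does not say which applies.

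**Step 5: group contrast.** All inputs are assumed: 0–100 scale, baseline mean 40 and SD 20, two-month gain mean 8 and SD 4, 200,000 simulated children per arm, second calculation with equal windows. The change is (N − S)/2 points per month.
- Equal baselines, true difference 4 points: the expected contrast is 4/2 = 2.0. The simulation gives 2.0 with the scale maximum imposed and 2.0 without.
- One arm 10 points higher at baseline, no therapy effect: the expected contrast is −10/2 = −5.0. The simulation gives −5.0 with the maximum and −4.9 without.

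So the bias between groups comes almost wholly from using the entire baseline score as the pre-rate. The scale maximum adds very little.

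**The case against.** The second calculation is openly adverse. Section 4 says that it limits the chance of the later values overtaking the earlier ones, and it is reported beside the first calculation as a worst case. That stands, and it is a reason to keep it. But the disclosure describes a difficulty that grows with age, whereas above the cut-off improvement is impossible, and what decides this is score. Age is at best a proxy.

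A reader might infer that good baseline function is scored as therapy failure. The documents do not support this. They define no failure or responder category, and a forced slow-down falls on both arms, so it cancels in the group contrast when baselines are similar. A reader might also apply the half-scale limit to all rate outcomes. It belongs to the second calculation only; step 3 shows much higher cut-offs for the first. Nor is the scale maximum the main source of group bias, as step 5 shows.

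Children with nothing left to gain would dilute a group difference on any bounded scale, including a raw change score. That is correct, so dilution is not specific to the rates. The share of such children is not in the article.

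Finally, the handling of completed dimensions could sit in an analysis plan that is not shown. A missing rule alone would be no finding. Here, however, the article itself fixes both rate definitions and extends them to every dimension, and the forced result follows from those definitions.

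**Conclusion.** The point holds in limited form. As written, a dimension completed at baseline must show a slow-down. With equal windows, a child older than two months who holds half the scale or more cannot exceed the maximal pre-rate; the cut-off is 0.47 to 0.53 of the maximum across the permitted visit window, if the pre-window stays at two months. These results need only the article's definitions and a finite item list.

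What they distort is the pre/post reading and the dimension results. Bias in the group contrast is conditional on a baseline difference between arms, which the allocation method makes possible but which the article does not show. The overall size cannot be computed, because the article gives neither the baseline distribution nor the share of completed dimensions; the figures in step 5 illustrate a mechanism and are not an estimate. The text should be changed before analysis. Section 4 reports completed data for only four children, so this can still be done before results are known.

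**What to change.** In section 4:
1. Calculate and compare dimension rates only among children with uncompleted items in that dimension at baseline, and report the number left out per arm and dimension.
2. Adjust the group comparison for baseline score and age. In the second calculation the pre-rate is a fixed multiple of baseline score, so a linear adjustment for that score removes it from the group contrast.
3. Keep the second calculation for all eligible children as a worst-case bound. State how many in each arm could not arithmetically exceed it, and do not read their result as evidence against an effect.

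Two alternatives are less attractive. Points gained over points still open is unstable near the top (1 of 2 open points counts as 50%) and leaves the rate construct of section 2.6. Dropping children above half the scale from the second calculation would tilt a deliberately conservative check toward a positive result.

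The cost is wording only: the planned dimension rates already require dimension scores, and age is recorded. The downside is that fewer children contribute to the early dimensions.

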#### 2.3.1. Inclusion Criteria

Male and female children between 0 and 36 months, with a risk of neurological alteration or diagnosis of cerebral palsy or neuromotor disease, who are admitted for assessment and/or treatment according to the Vojta therapy methodology or conventional treatment in the Physical and Rehabilitation Medicine Service will be included in this study. The diagnosis may be clinical and/or supported by the presence of lesions in complementary tests. Due to the fact that the diagnosis of cerebral palsy is confirmed in many cases after one year of life, the data of children in treatment for risk of neurological alteration will only be included retrospectively when said diagnosis has been confirmed. Younger children have not received a definite diagnosis of CP yet, but, based on the presence of lesions determined by magnetic resonance imaging, their risk of developing CP was estimated to be sufficiently high to justify their inclusion in the CP group. 

Parents or guardians must sign the informed consent that will allow us to use their data on therapeutic results, always in a pseudonymized (coded) way, guaranteeing confidentiality. 

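### In a GMFM dimension scored 0 at baseline, every pre-treatment rate is 0, so one new point exceeds it and the within-child comparison cannot be unfavourable

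*Protocol article*

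**What the plan says.** All the definitions are in Section 4 (Discussion and Ethical–Legal Aspects) of the protocol article.

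- Average pre-treatment rate: "The rate values are calculated by dividing the total score by the time (days of age) required to achieve it". The score at birth is taken to be zero.
- Maximal pre-treatment rate, for children older than two months at the initial assessment: "we performed a second rate calculation assuming that all the items were adquired during the last two months before the intervention".
- Post-treatment rate: "Only new points acquired during this period were considered to calculate the rate of development and acceleration values in the intervention period".
- Purpose of the maximal rate: "This simulation of the maximal possible pre-intervention rate and acceleration will limit the possibility of being overcome by the post-treatment values".
- Inference to be drawn from the two pre-treatment rates: "both calculations will help us to understand if the rate differences are due to natural acceleration or a significant therapeutic change".
- Extension to dimensions: "Rate values within each GMFM dimension will then be considered and will help to clarify the results".

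Acceleration is derived from each rate by dividing by elapsed time. The article gives no rule for a dimension with a baseline score of 0. Section 2.3.2 supports the within-child reading, because it justifies its handling of earlier and concomitant treatment by saying that each child serves as their own comparator. The Statistical Methods part of Section 3 separately names a repeated-measures ANOVA with time and treatment group as factors.

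**The concern.** The maximal pre-rate is meant to be a hard bar, so that ordinary growth is not read as a treatment effect. Its height is set by the points the child already holds. For a total score well above zero the bar is high. In a dimension the child has not begun there are no points, so the bar is at zero whatever the child's age.

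Unstarted dimensions are plausible here. The inclusion criteria in Section 2.3.1 cover "Male and female children between 0 and 36 months", the children have or are at risk of a neuromotor disorder, and the article itself sets the score to zero at birth. These are also the dimensions in which new milestones would first appear, and Section 4 ties its interpretation to the onset of motor function. A child who gains a first point through ordinary development would be recorded as having exceeded the highest rate thought possible before treatment.

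**Working it through.** **Inputs**
- S: baseline points in the dimension (or in total).
- A: age in days at baseline (Section 4).
- T: the intervention window. Section 3 gives 2 months ±1 week, taken here as 60 days (range 53–67). The same 60 days are used for the two months before treatment.
- G: new points gained during the window.

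**Formulas from Section 4**
- Average pre-rate = S/A
- Maximal pre-rate = S/T
- Post-rate = G/T
- Acceleration = rate divided by elapsed days

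The maximum is exceeded when G/T > S/T, that is, when G > S.

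**Step 1: S = 0.** At ages 90, 180, 365, 730 and 1095 days, the average pre-rate is 0/A = 0 and the maximal pre-rate is 0/60 = 0. Both pre-accelerations are 0. With G = 1, the post-rate is 1/60 = 0.0167 per day (1/67 = 0.0149 to 1/53 = 0.0189 over the visit window), and the acceleration is 0.0167/60 = 0.00028 per day². One point exceeds everything it is compared with. With G = 0 the result is a tie. No outcome is unfavourable.

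**Step 2: S > 0.** To exceed the maximum the child must gain S + 1 points: 2 if S = 1, 6 if S = 5, 21 if S = 20, 41 if S = 40. The bar is therefore real in well-established dimensions and in the total score, and low in a dimension just begun.

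**Step 3: one illustrative child.** All values are assumed: age 365 days, five dimensions, baseline 25/10/5/0/0, gains 3/2/1/1/0.

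| | S | G | Average pre-rate | Maximal pre-rate | Post-rate | Exceeds maximum? |
|---|---|---|---|---|---|---|
| Dimension 1 | 25 | 3 | 0.0685 | 0.417 | 0.050 | No |
| Dimension 2 | 10 | 2 | 0.0274 | 0.167 | 0.033 | No |
| Dimension 3 | 5 | 1 | 0.0137 | 0.083 | 0.017 | No |
| Dimension 4 | 0 | 1 | 0 | 0 | 0.017 | **Yes** |
| Dimension 5 | 0 | 0 | 0 | 0 | 0 | No (tie) |
| Total | 40 | 7 | 0.110 | 0.667 | 0.117 | No |

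The only dimension to exceed its maximum is the unstarted one with a single new point.

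**Step 4: how many children.** The article gives no baseline dimension scores, so this step rests on assumptions: baseline age uniform over 2–36 months; development at 0.2–1.0 of typical speed; five 50-point dimensions with successive starting ages (several sets tried) and linear growth within each; two months of follow-up; no treatment effect. Across these runs, about 17–24% of simulated children exceeded the maximum through a dimension that was at 0.

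**Step 5: effect on the arm comparison.** With the same kind of growth model, 30 children per arm, balanced allocation and no treatment effect, the arm contrast of post-rate minus maximal pre-rate was tested in each dimension. The false-positive rate was 4.7–5.2%, in line with the nominal 5%.

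**The case against.** **The maximal rate by dimension is inferred.** Section 4 defines the rate on the total score, and the dimension sentence speaks only of rate values. This is correct: nowhere does the article say outright that the maximal rate is recomputed by dimension. It is still the natural reading, because the sentence follows directly on the two calculations. If only the average rate is meant, that is also 0 in an unstarted dimension and the defect remains.

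**Dimension results are supportive.** No goal or named test rests on them, the sentence sits in the discussion, and it could describe no more than a look at where points were gained. This stands and limits the importance of the point. It does not turn the point into detail left to an analysis plan, because the article itself fixes the formulas and states what they are for.

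**The ANOVA has a concurrent control arm.** This also stands. A reader might infer that the floor biases the Vojta comparison. The documents do not support that: growth from zero occurs in both arms, and Step 5 shows no inflation under balance. Bias between arms needs an imbalance in unstarted dimensions. Allocation by therapist availability (Section 2.3) does not rule this out, but nothing in the article shows it.

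**The safeguard is not lost everywhere.** A reader might infer that it fails for dimensions in general. It does not: a started dimension still requires more points in two months than in the child's whole earlier life.

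**The size is assumed.** A reader might want a multiplier for how much more often the safeguard fails by dimension than on the total score. None is supportable. It would set a count over any of five dimensions against a single comparison, and it would depend on invented starting ages and speeds.

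**Conclusion.** The point holds for the within-child comparison. For a dimension scored 0 at baseline, the average pre-rate is exactly 0 at any age, and so is the maximal pre-rate if it is applied by dimension. One new point exceeds both, and the comparison cannot come out against treatment. Dimension rates therefore cannot separate natural acceleration from a therapeutic change in such a child. The arithmetic follows from the article's own definitions and needs no further assumption.

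Its reach is limited. It does not touch the total-score safeguard, it weakens that safeguard only partly in dimensions just begun, and by itself it does not bias the arm contrast. The figure of 17–24% of children is an order of magnitude resting on the assumed growth schedules. It is not an estimate for this trial. The text should be changed, but the main between-arm analysis does not depend on it.

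**What to change.** Amend the rate paragraph in Section 4, and carry the change into any analysis plan, as follows:

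1. Do not apply the pre/post rate, acceleration or maximal comparison to a dimension in which the child's baseline score is 0.
2. For dimensions, compare the arms on points gained over the two months, adjusted for baseline dimension score and age. Children with a zero baseline stay in this comparison.
3. Report the dimension results as descriptive or supportive, and do not use dimension rates to separate natural from therapeutic change within a child. This also covers dimensions just begun.
4. State whether the maximal rate is calculated by dimension at all.

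The cost is wording only, since the planned GMFM assessments already supply the data. Section 4 reports completed assessments for four subjects, so the rule can still be fixed before results are examined. The downside is fewer child-by-dimension pairs in the within-child comparison. The adjustment in item 2 deals with imbalance in baseline dimension score and age only; it does not make up for allocation by therapist availability in other respects.
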